## Abstract

**Background:**

Rates of cesarean delivery are continuously increasing in industrialized countries, with repeated cesarean accounting for about a third of all cesareans. Women who have undergone a first cesarean are facing a difficult choice for their next pregnancy, i.e.: (1) to plan for a second cesarean delivery, associated with higher risk of maternal complications than vaginal delivery; or (b) to have a trial of labor (TOL) with the aim to achieve a vaginal birth after cesarean (VBAC) and to accept a significant, but rare, risk of uterine rupture and its related maternal and neonatal complications. The objective of this trial is to assess whether a multifaceted intervention would reduce the rate of major perinatal morbidity among women with one prior cesarean.

**Methods/design:**

The study is a stratified, non-blinded, cluster-randomized, parallel-group trial of a multifaceted intervention. Hospitals in Quebec are the units of randomization and women are the units of analysis. As depicted in Figure 1, the study includes a 1-year pre-intervention period (baseline), a 5-month implementation period, and a 2-year intervention period. At the end of the baseline period, 20 hospitals will be allocated to the intervention group and 20 to the control group, using a randomization stratified by level of care. Medical records will be used to collect data before and during the intervention period. Primary outcome is the rate of a composite of major perinatal morbidities measured during the intervention period. Secondary outcomes include major and minor maternal morbidity; minor perinatal morbidity; and TOL and VBAC rate. The effect of the intervention will be assessed using the multivariable generalized-estimating-equations extension of logistic regression. The evaluation will include subgroup analyses for preterm and term birth, and a cost-effectiveness analysis.

**Discussion:**

The intervention is designed to facilitate: (1) women’s decision-making process, using a decision analysis tool (DAT), (2) an estimate of uterine rupture risk during TOL using ultrasound evaluation of low-uterine segment thickness, (3) an estimate of chance of TOL success, using a validated prediction tool, and (4) the implementation of best practices for intrapartum management.

**Trial registration:**

Current Controlled Trials, ID: ISRCTN15346559. Registered on 20 August 2015.

**Electronic supplementary material:**

The online version of this article (doi:10.1186/s13063-017-2150-x) contains supplementary material, which is available to authorized users.

## Background

Compared to historical rates, the rate of cesarean deliveries is high in industrialized countries. In Canada, these rates increased from 21.2 to 28.0% between 2000 and 2008 and remained stable since 2011 [1–3]. Previous cesarean deliveries alone are an indication for over 30% of all cesareans in Canada. Every year, over 30,000 women in Canada who have undergone a cesarean delivery will be faced with a difficult choice for their next pregnancy, i.e.: (1) plan for a second cesarean delivery, associated with a higher risk of maternal complications than a vaginal delivery [4, 5], or (2) have a trial of labor (TOL) to achieve a vaginal birth after cesarean (VBAC) and accept a significant, but rare, risk of uterine rupture [6–9], which constitutes a principal complication related to a TOL [10–16]. However, although an elective repeat cesarean (ERC) may prevent uterine rupture in most cases, this intervention is associated with a higher risk of maternal and perinatal complications, particularly compared to a VBAC [4, 16–21]. The choice of the mode of delivery among women with a prior cesarean delivery constitutes an important public health issue within the current context, in which health professionals hesitate, due to a variety of reasons – including the risk of litigation – to recommend a TOL in the absence of validated and effective methods that can predict the risk of uterine rupture [22, 23].

Recently, new clinical tools have been developed to assist in women’s decision-making [24], including those that help estimate the chance of TOL success [25–27], and the risk of uterine rupture [16, 28–30]. Several RCTs performed in pregnant women and a recent meta-analysis [24], demonstrated that decision analysis tools (DAT) are effective in improving women’s knowledge; reducing anxiety and decisional conflict; and guiding women’s final choice during the decision-making process [31–44]. Based on a study involving 9616 women attempting VBAC in United States, Grobman et al. developed a nomogram to assess the chances of TOL success based on *antepartum* clinical factors and factors available upon admission at the time of delivery [25, 26]. Two observational studies and the recent statements of the NIH Consensus Development Conference confirmed the validity of this instrument in North America [16, 45–47]. Grobman et al. also highlighted that a prediction model for TOL success provides also additional information regarding the chance of TOL-related morbidity. They showed that maternal and neonatal morbidity is not greater for those women who undergo TOL than for those who undergo an elective repeat cesarean delivery when the chances of VBAC success are at least 70% [48]. Finally, two observational studies in Québec, along with a meta-analysis, assessed the effectiveness of measuring the lower uterine segment thickness (LUS) by ultrasound between the 35 and 38 week of pregnancy, to estimate the risk of uterine rupture [28, 29, 49]. Findings indicated: (1) the combination of abdominal and endovaginal ultrasounds allowed an optimal detection rate for uterine scar defect; [50, 51], (2) a LUS thickness < 2.0 mm represent a higher risk of uterine rupture (>1%), a LUS thickness ≥ 2.0 and < 2.5 mm represent a moderate risk of uterine rupture (around 0.5%), and a LUS thickness ≥ 2.5 mm represent a low risk of uterine rupture (<0.3%); [49] and (3) the use of LUS thickness in clinical practice was associated with no symptomatic uterine rupture among 984 women who underwent a TOL after one prior cesarean delivery [49], compared to 0.36% in the meta-analysis of Guise et al. [16]. These results were confirmed by a recent meta-analysis on the effect of the LUS method on uterine rupture (OR = 0.19; CI 95% = 0.09 to 0.40) [29], supporting the hypothesis that the LUS method, performed between the 35 and 38 week of pregnancy, is currently the most effective instrument to predict uterine rupture in women with previous low-transverse cesarean [28, 29, 49].

The availability of new, validated and standardized tools may facilitate the decision-making process as they may assist in the prediction of TOL success as well as of uterine rupture [24, 28, 29, 49]. However, their effectiveness in leading to an optimal selection of women for a TOL remains uncertain. This trial was designed to assess whether a multifaceted intervention based on the implementation of these tools into clinical practice (PRISMA program) will reduce the rate of major neonatal morbidities among women with one prior cesarean delivery.

### Hypothesis

Our primary hypothesis is that women exposed to the PRISMA program (Process for decision-making, RISk assessment and MAnagement in obstetrics) will have a rate of major perinatal morbidity, as measured in the hospitals during the intervention period, that is reduced by 25% in comparison with the control group (relative reduction). Secondary hypotheses are that the PRISMA program will: (1) reduce the rate of major maternal morbidity, (2) reduce the rate of minor maternal and perinatal morbidity, and (3) increase the rate of VBAC.

## Methods/Design

### Study design

This is a non-blinded, multicentre, stratified, cluster-randomized, parallel-group trial in which hospitals are the units of randomization and patients are the units of analysis. Randomization will be stratified according to level of care (community, regional, or tertiary hospital). The study included a 1-year pre-intervention (baseline) period, a 5-month implementation period, and a 2-year intervention period (Fig. 1).

**Fig. 1 Fig1:**
[figure not shown]
SPIRIT schedule for trial preparation, pre-intervention, intervention and assessments

### Inclusion and exclusion criteria

All hospitals entered the trial in April 2016. The study is conducted in 40 out of 48 eligible public hospitals in the province of Québec. To be eligible, each center was required to offer TOL after cesarean in their population; to have a minimum of 300 deliveries in the previous year; to have functional operating rooms; to have access to a high-performance sonographic device; and at the time of recruitment, to have no recent or ongoing quality-improvement programs specifically designed to target women with one prior cesarean delivery. Hospitals where LUS thickness measurement was already available in routine clinical practice and will remain available during the study were excluded from the trial.

At the patient level, women with only one prior cesarean delivering at one of the participating centers at a minimum of 24 weeks with one newborn who weighs at least 500 g at delivery are included in the analyses. Women with delivery or miscarriage before 24 weeks of gestation, with more than one previous cesarean delivery or with multiple gestations will be excluded from the trial.

### Intervention group activities

Intervention group activities will start in April 2017 and will end in August 2019. The PRISMA program, which will be implemented at the hospital level in the intervention group, targets physicians and nurses involved in the decision-making process for an ERC or a TOL among women with one prior cesarean delivery. The PRISMA program consists of: (1) a decision-aid tool to support women’s decision making in the choice of the mode of delivery (DAT), (2) standardized risk assessment tools leading to an optimal selection of women eligible for a TOL, i.e.: (a) an estimation of the chance of vaginal birth after cesarean (VBAC) success (Grobman nomogram), and (b) an estimation of the risk of uterine rupture using ultrasound measurement of lower uterine segment (LUS) thickness, and (3) a professional training program from the Society of Obstetricians and Gynaecologists of Canada (SOGC) to describe an optimal management of delivery and labor dystocia for a TOL. No financial incentive will be provided.

#### Professional training program from the SOGC

The 5-month implementation period will focus on implementing the PRISMA program in each of the 20 hospitals randomized to the intervention group. In each centre receiving the intervention, health professionals in obstetrics (physicians, nurses qualified in obstetrics, and midwives, if available) will be invited to participate in an onsite 1-day training workshop, provided by certified instructors from the Society of Obstetricians and Gynaecologists of Canada (SOGC), on best practices regarding intrapartum management among women with one prior cesarean delivery, as well as on the PRISMA clinical prediction tools. Using SOGC clinical practice guidelines and algorithms, health personnel will be trained on the following topics: prolonged pregnancy, management of the first and the second stages of labor, induction and stimulation of labor, fetal health surveillance, use of the WHO partograph [52], and assisted vaginal delivery. The SOGC training program will also include a workshop on the criteria to be assessed and discussed with the women during the decision-making process, as well as on the clinical use and interpretation of the Grobman prediction tool and of the ultrasound evaluation of the risk of uterine rupture. The training program will also sensitize participants to maternal factors contributing to the choice of the mode of delivery. Finally, in each hospital receiving the intervention, one or two technicians and physicians, with expertise in sonography, will be identified and invited to receive additional 1-day training in sonographic techniques related to the evaluation of the risk of uterine rupture. A half-day of recertification will be scheduled at the beginning of the second year of the intervention period. The entire training program will be overseen by the SOGC, which possesses extensive expertise in the field of professional training [53]. Details of the training program and algorithms will be available after the trial (September 2019) upon request by email to the corresponding author (NC).

#### Implementation of clinical tools leading to an optimal selection of women eligible for a TOL

After the 5-month implementation period, physicians from the intervention hospitals will be asked to use the three clinical tools of the program that assess the women’s initial preferences (DAT), the risk of uterine rupture (LUS) and the chances of TOL success (Grobman nomogram) for a period of 2 years from September 2017 to August 2019 (intervention period).

##### Decision analysis tool

The DAT used in this trial, entitled “Giving Birth after Cesarean Section: Making an Informed Choice”, has been adapted from the A. Shorten Birth Choices study [43], validated in Quebec in 2011 [54], and has received a 96% ranking on the International Patient Decision Aid Standard (IPDAS) assessment scale [55, 56]. The DAT is divided into two sections: (A) an Information section, providing a description and an explanation of the risks and benefits of each option, and (B) an Exercise section, allowing women to clarify and summarize their values and preferences with their physician about the choice of the mode of delivery, indicating what suggestions are important and how important these suggestions are (not important, important, very important). The DAT will be distributed between 12 ^0/7^ and 34 ^6/7^ weeks of pregnancy by the treating physician, preferentially early in the pregnancy, to all women with one prior cesarean delivery during their follow-up visit. The physician will ask the women to read the DAT carefully and complete the Exercise section, so that they will be able to discuss their preferences during their next appointment.

##### Grobman nomogram

Antepartum assessment of the chances of TOL success among women with one prior cesarean delivery will be conducted by the treating physician between 12 ^0/7^ and 34 ^6/7^ weeks of pregnancy, during one of the patient’s follow-up visits [25]. The treating physician will use the Grobman nomogram, derived from logistic regressions, which generates probability of VBAC success and a confidence interval of 95% [25–27, 46, 47]. This tool is based on maternal characteristics available at the time of the first prenatal visit, i.e. maternal age, Body Mass Index, prior vaginal delivery, prior successful VBAC, and recurrence of indication of prior cesarean delivery [25]. The assessment will then be completed after 36 ^6/7^ weeks of pregnancy, according to the maternal characteristics available at the time of admission, i.e.: estimated gestational age at delivery; hypertensive disease of pregnancy; labor induction; effacement; dilation; and station [26]. Results related to VBAC success and risk level will be discussed with each woman during their pregnancy and upon admission for delivery.

##### Ultrasound assessment of the risk of uterine rupture (LUS clinic)

The treating physician will routinely refer eligible women to the LUS clinic between 35 ^0/7^ and 38 ^6/7^ weeks of pregnancy. Each woman will meet with a nurse who will verify her eligibility, and will obtain her consent to the LUS. Eligibility criteria for the sonogram include: one prior cesarean delivery, and no uterine incision or laceration other than lower transverse; no multiple gestation; no known lethal congenital abnormalities; no preterm rupture of membranes; and no labor at the time of sonography. After ensuring that the woman has a full bladder, a trained ultrasound technician or a physician will measure the lower uterine segment (LUS) thickness by abdominal and endovaginal ultrasounds. The lower uterine segment will be swept in a sagittal cut from the right extremity to the left extremity, with the probe placed to detect the thinnest area of the lower segment. The technician/physician will also record the amniotic fluid index, the biparietal diameter, the cranial and abdominal circumference and the femoral length, in order to estimate the fetal weight. For each of the abdominal and endovaginal ultrasounds, the technician/physician will capture three pictures and a 15-s film (2D-ultrasound in real time).

Each 15-s film will be then immediately sent to a centralized platform in Québec in order to allow an external validation of each film in less than 1 h by experienced experts in measurement of the LUS thickness. This continuous training platform will accelerate the learning curve among health professionals in hospitals from the intervention group. The technicians of the centralized platform will capture three total measurements of the thinnest lower segment for each of the abdominal and endovaginal ultrasounds, based on the two 15-s films, and then send the results to the physician of the LUS clinic at the referring hospital. Once the measurements have been taken and the results of the external validation in Québec are available, the physician responsible of the LUS clinic, who has also been trained, will validate the exam and reproduce it immediately, as required. Only the thinnest measurement, from among the six measurements taken via the abdominal and endovaginal ultrasounds, will be used. For each professional, a continuous quality assessment of the measurement, based on objective criteria, will be conducted during the first 30 measurements of the LUS thickness. Additional training could be considered depending on the performance of each professional [28, 50, 51, 57–59].

The physician in charge of the LUS clinic will complete a consultation form to be sent to the treating physician. The treating physician will be informed of the estimated fetal weight (EFW) and the risk of uterine rupture and will discuss the results with the woman. According to lower uterine segment thickness, women will be classified into three risk categories for uterine rupture: high risk (< 2.0 mm), intermediate risk (≥ 2.0 mm and < 2.5 mm), and low risk (≥ 2.5 mm). If the EFW falls below the 95th percentile and the LUS thickness is ≥ 2.5 mm, the treating physician will be informed that the risk of uterine rupture is < 0.3% in the absence of labor induction with unfavorable cervix, and that a TOL should be recommended in the absence of other contraindications [16, 28, 29, 45, 60–62]. If the LUS thickness is < 2.0 mm, the treating physician will be informed that the risk of uterine rupture is > 1%, and that a TOL should not be considered except in exceptional circumstances (e.g. admission at full cervical dilatation). If the LUS thickness is ≥ 2.0 and < 2.5 mm, the treating physician will be informed that the risk of uterine rupture is intermediate (around 0.5%), and that a TOL could be considered if no other particular conditions are observed. The exact LUS thickness, however, will not be conveyed to the patient or treating physician.

### Control group

No intervention from the PRISMA team is planned for the control group. In order to assess contamination bias, quality-improvement programs will be reviewed annually in control hospitals.

### Study outcomes

The primary outcome is the major perinatal morbidity rate. The composite risk of major perinatal morbidity includes: (1) In utero, intrapartum and neonatal death, defined as the fetal death in utero, during labor or prior to 28 days of age (excluding lethal congenital abnormalities); (2) APGAR score at 5 mn < 4; (3) Metabolic acidosis (umbilical arterial pH < 7 + base excess ≤ −12 mmol/l); (4) Major trauma (skull fracture, subdural/subarachnoid haemorrhage, brachial plexus injury, spinal cord injury, major genital injury, paresis/paralysis at discharge); (5) Intracerebral/intraventricular haemorrhage (grades 3 and 4); (6) Periventricular leukomalacia; (7) Seizure (occurring from delivery to discharge); (8) Invasive mechanical ventilation with endotracheal intubation; (9) Major respiratory morbidity (bronchopulmonary dysplasia treated with oxygen or ventilation at 36 weeks post menstrual age or at 28 days of life, persistent pulmonary hypertension of the newborn, pneumothorax, pulmonary haemorrhage, hyaline membrane disease requiring mechanical ventilation); (10) Necrotising enterocolitis, stage 2 and 3; 11) Hypoxic-ischemic encephalopathy (APGAR 5mn < 4 + pH < 7 + base excess < −12 mmol/L + seizure); (12) Proven neonatal sepsis/infection (positive blood or cerebrospinal fluid culture); and (13) Hypotension requiring vasopressor support. The binary primary outcome (0; 1) event is triggered by occurrence any of the above morbidities. Value 1 is attributed if at least one of the above conditions is met.

Secondary outcomes include:
*The rate of major maternal morbidity:* this indicator is measured with a composite factor of maternal morbidity including: (1) maternal death (≤ 6 weeks postpartum); (2) hysterectomy; (3) proven thromboembolic complications (thrombophlebitis, pulmonary emboli); (4) admission to intensive care unit for ≥ 4 days; (5) acute pulmonary edema/cardiogenic shock; (6) sepsis with proven bacteremia (septicemia); (7) injury/lacerations to internal organs, requiring surgical repair (bladder, bowel, large vessels); (8) symptomatic uterine rupture (complete rupture of the uterine wall with extrusion of amniotic fluid, placenta, or fetal limb outside the uterine cavity, or with rupture of the bladder, requiring surgical repair)
*The rate of minor maternal morbidity:* this indicator is measured with a composite factor of maternal morbidity including: (1) blood transfusion; (2) postpartum hemorrhage requiring surgical procedure; (3) perineal tear of third or fourth degree; (4) cervical lacerations requiring repair; (5) dehiscence of skin wound (C-section or perineal); (6) puerperal fever (≥ 38 °C postpartum); (7) postpartum infection requiring drugs or surgery (infection of the incision (C-section or perineal), uterus (e.g. endometritis), urinary tract (≥ 10^5^ CFU/ml), respiratory tract (e.g. pneumonia)); (8) major gastrointestinal complications (intestinal occlusion); (9) obstetric anesthesia complications (neurological, cardiovascular, respiratory); (10) length of postpartum hospital stay ≥ 7 days; (11) admission to intensive care unit for less than 4 days; and (12) readmission to hospital within 40 days of childbirth
*The rate of minor perinatal morbidity:* this indicator is measured with a composite factor of perinatal morbidity including: (1) minor cardiorespiratory complications (cardiac rhythm disorders, delayed amniotic fluid clearance, transient tachypnea of the newborn); (2) non-invasive mechanical ventilation; (3) admission to the intensive care unit for less than 4 days; (4) oxygen therapy; (5) suspicion of neonatal infection (culture-negative); (6) APGAR score ≥ 4 and < 7 at 5 min; (7) acidosis (umbilical artery pH ≥ 7 and < 7.20); (8) minor trauma (lacerations, limb fracture, clavicle fracture); (9) transfusion in first 24 h; and (10) weight loss > 10% in first ten postnatal days
*Rate of trial of labour (TOL):* this is the number of women attempting a vaginal delivery divided by the total number of women with one previous C-section
*Rate of VBAC:* this is the number of vaginal deliveries divided by the total number of women with one previous cesarean delivery

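### Neonatal intensive care stays of 4 days or more count in neither perinatal composite, so an infant with no other listed item scores lower for a longer stay

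*Protocol article*

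**What the plan says.** All definitions are under Study outcomes in the protocol article.

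- **Major perinatal morbidity (primary).** The list opens with "The composite risk of major perinatal morbidity includes: (1) In utero, intrapartum and neonatal death" and closes with "12) Proven neonatal sepsis/infection (positive blood or cerebrospinal fluid culture); and (13) Hypotension requiring vasopressor support". It has 13 items and is followed by the scoring rule "Value 1 is attributed if at least one of the above conditions is met". No item is an intensive care admission or a length of stay.
- **Minor perinatal morbidity (secondary).** Ten items, among them "3) admission to the intensive care unit for less than 4 days; (4) oxygen therapy".
- **Maternal composites.** The major list has "4) admission to intensive care unit for ≥ 4 days". The minor list has the complementary item, a stay of under 4 days.
- **Acidosis in the newborn.** The major item begins "Metabolic acidosis (umbilical arterial pH" and requires a value below 7 together with a base excess of −12 mmol/l or lower. The minor item covers an umbilical artery pH from 7 up to, but not including, 7.20.

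Under Hypothesis, a reduction in minor maternal and perinatal morbidity is a stated secondary hypothesis. Under Statistical analysis, secondary outcomes are to be analysed with methods similar to those for the primary outcome.

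**The concern.** The two perinatal composites work as a severity pair. Several minor items stop where a major item takes over: 5-minute APGAR, invasive against non-invasive ventilation, culture-positive against culture-negative infection. For intensive care the minor item has an upper bound and nothing lies above it. An infant can therefore leave the minor outcome by doing worse, without entering the major one.

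At stake is the direction of the minor perinatal result. Take infants with no other listed item. If the programme shortens their stays from 4 days or more to under 4, the minor rate rises and looks like harm. If it lengthens them past 4 days, the rate falls and looks like benefit. The economic evaluation also plans to break costs down into categories that reflect the secondary outcomes, and these definitions do not capture long intensive care stays as such.

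**Working it through.** The article states no figure that depends on this point, so there is none to reproduce. The check is to score the items as written.

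**Step 1. Intensive care item alone.** Let d be the stay in days. The minor item scores 1 if 0 < d < 4. The major composite has no corresponding item.

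| Stay | Major perinatal | Minor perinatal | Mother, same stay: major / minor |
|---|---|---|---|
| none | 0 | 0 | 0 / 0 |
| 2 days | 0 | 1 | 0 / 1 |
| 3.9 days | 0 | 1 | 0 / 1 |
| 4 days | 0 | **0** | 1 / 0 |
| 10 days | 0 | **0** | 1 / 0 |
| 30 days | 0 | **0** | 1 / 0 |

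The maternal columns never return to 0 / 0 as the stay lengthens. The perinatal columns do, at 4 days.

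**Step 2. When this changes the infant's score.** Each composite is 1 if any of its items is met. The table therefore gives the infant's overall result only when none of the other 22 listed items (13 major, 9 other minor) is met. An infant on oxygen or non-invasive ventilation, or with suspected infection, already scores 1 on the minor outcome. One who was intubated already scores 1 on the major outcome.

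**Step 3. Acidosis items alone.**

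| Umbilical artery pH | Base excess (recorded) | Major item | Minor item |
|---|---|---|---|
| 7.15 | any | 0 | 1 |
| below 7 | −12 or lower | 1 | 0 |
| below 7 | above −12 | **0** | **0** |

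The hypoxic-ischemic encephalopathy item does not fill the third row, because it too requires a base excess below −12.

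**Step 4. Direction and scale.** Sample size and power calculation expects 7,360 women a year, so the 2-year intervention period has 2 × 7,360 = 14,720, or about 7,360 per arm if the arms are equal in size. If k infants in the residual group of one arm move from 4 days or more to under 4, that arm's minor rate changes by +k/7,360. With k = 10 this is 10/7,360 = 0.14 percentage points upward, although stays became shorter. If any stay counted, the change would be 0.

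The article does not give the size of the residual group. Purely as an assumption, 0.5% to 2% of infants would be 14,720 × 0.005 = 74 to 14,720 × 0.02 = 294, over both arms together. Nothing in the article supports either end. The count is also not the bias: under the planned difference-in-differences analysis, what matters is how the split across the 4-day line changes between periods in one arm relative to the other.

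**The case against.** **Most long-stay infants will be counted anyway.** This stands in large part. The other items catch many of them, and the article gives no figures for the remainder. A reader might infer that any infant kept longer is scored as healthier; the text supports this only for infants with no other listed item.

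**A minor composite need not rise with severity.** This also stands. The APGAR and pH items are capped so that worse cases pass to the major list, and an improvement from major to minor properly raises the minor rate. The fault is only that the cap on intensive care has no upper counterpart, and that the cap on pH has an incomplete one.

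**The pH and base excess requirement is a deliberate definition of metabolic acidosis.** That is accepted, and the major item need not change. Infants between the two definitions still fall out of both. A reader might go further and say that infants with no recorded base excess score 0; the article gives no such rule, and the handling of missing components may lie in documents not shown.

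**The maternal pattern would put long stays in the major list.** A reader might infer that a major perinatal item was dropped by mistake and that the primary outcome is faulty. The parallel suggests this, but the article does not state the intent. The 13-item list is explicit and has its own scoring rule, so the primary outcome can be applied as written.

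**The full protocol or analysis plan may settle it.** It may, but the article gives complete numbered lists with explicit bounds, and the gap follows from those bounds.

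**Conclusion.** The gap is real and follows from the wording alone. Neonatal intensive care stays of 4 days or more are in neither composite, and an infant with such a stay and no other listed item scores below the same infant with a shorter stay. In that group, movement across the 4-day line shifts the minor perinatal rate the wrong way. The acidosis gap is of the same kind and narrower: pH below 7, a recorded base excess above −12, and no other listed item.

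The effect on the result cannot be sized from the article and may be small. It touches one secondary composite. The primary outcome, its assumed 4.5% rate and the power calculation are unaffected. The definition should be corrected because the direction of error is known and the correction is simple.

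**What to change.** By a documented amendment made before the comparative analysis, and applied to both periods and both arms:

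1. Change minor perinatal item 3 to *admission to the intensive care unit of any duration*.
2. Change minor perinatal item 7 to *umbilical artery pH < 7.20 not meeting the major acidosis definition*.
3. Leave the primary composite unchanged, and state that omitting stays of 4 days or more from it is intended. Adding such an item instead would change the primary outcome and could move its rate away from the assumed 4.5%.

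The cost is modest. Hospitals are already randomised (Trial status), so the change must be dated and justified as an amendment. Outcomes are abstracted from medical records at least 3 months after delivery, in the same way in both arms, so baseline and intervention records can be scored alike. If the case report form holds only a yes/no for stays under 4 days, records already abstracted would have to be reopened for this item. The minor rate becomes slightly higher, and a long stay on its own counts as minor, unlike in the maternal split; the amendment should say so.
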